### Sample size

The main end-points are six and 24 months [12]. From clinical experience we estimated that the smallest clinically important detectable difference is 10 points on the 100 points Rowe Score. Assuming that the largest difference between treatments will be 10 units, we simulated multiple scenarios and estimated the standard deviation between means to be 14.6 units. To detect this difference between treatment groups (SD = 15, α = 0.05, β = 0.80, One-Way ANOVA) our study will require 36 patients in each group. Assuming some patients drop-out, we plan to include 40 patients in each group.

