### Planned statistical analysis

Treatment groups will be examined for comparability at baseline with respect to demographic and prognostic factors. All eligible patients, regardless of their compliance with protocol (analysis by intention-to-treat) will be included in the main analyses. To asses the effect of the interventions on the endpoints (six and 24 months), analysis of covariance (ANCOVA) will be performed using the baseline values as one of the covariates. Standard regression assumptions will be assessed using diagnostic plots, Jacknife residuals, Cook's distances, and Variance inflation Factor (VIF). We will adjust for an eventual imbalance at the baseline. Corresponding post-hoc tests (Tukey's test) will be performed. To evaluate the time-course at three, six, 12, and 24 months, repeated measures will be analyzed using linear mixed models. If the number of missing values exceeds 10% in one of the groups, multiple imputations will be used to estimate the missing values. To assess the robustness of our findings the analysis will be performed with and without the imputed values.

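### The sample-size paragraph gives an impossible SD between means and mislabels the power, and its 80% holds only if two of the three group means nearly coincide, which it does not state

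*Protocol article*

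**What the plan says.** The Sample size section of the protocol article sets the target from clinical experience: "the smallest clinically important detectable difference is 10 points on the 100 points Rowe Score". The same 10 points are then taken as the greatest gap among the three group means. On the spread of those means the authors report that "we simulated multiple scenarios and estimated the standard deviation between means to be 14.6 units". The calculation is specified as "SD = 15, α = 0.05, β = 0.80, One-Way ANOVA", with the result that "our study will require 36 patients in each group". An allowance for losses follows: "Assuming some patients drop-out, we plan to include 40 patients in each group". No drop-out rate is given; 36/40 implies 10%.

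The section does not say where the third group mean lies between the two extremes.

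Under Planned statistical analysis, the six- and 24-month endpoints are to be analysed by ANCOVA with the baseline value as a covariate. For the pairwise comparisons: "Corresponding post-hoc tests (Tukey's test) will be performed". No power is given for these tests and no baseline-to-follow-up correlation is stated.

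**The concern.** Two entries cannot be right as printed. An SD among three means cannot exceed the range of those means, so 14.6 is incompatible with a largest difference of 10. And β is the type II error, so a β of 0.80 would mean 20% power.

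These are the inputs that carry the sample size. The power of a three-group ANOVA depends on how all three means are spread, not only on the largest gap. If the SD between means is wrong and no pattern is given, a reader cannot tell which scenario the 80% belongs to.

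What is at stake is how a non-significant result would be read. The aims compare two operations with placebo and with each other, and a global F test does not say which groups differ. The Discussion cites sham-controlled surgical trials with null results, so a null result is a realistic prospect here. A reader will tend to attach 80% to any 10-point contrast between treatments.

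**Working it through.** **Inputs from the protocol.** Three equal groups; largest difference 10; SD 15, taken as the within-group SD; α = 0.05; power 0.80; 36 per group required, 40 planned. **Assumptions of this check.** The middle mean is varied, because it is not stated. Pairwise tests are two-sided. Baseline correlations are assumed.

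**1. Reproducing 36.** Two routes reach it.
- Two-group normal formula: n = 2 × (1.960 + 0.842)² × (15/10)² = 2 × 7.849 × 2.25 = 35.3, so 36. The exact t-test gives 37.
- Three-group one-way ANOVA (noncentral F), n for 80% power: 34 for means (0, 0, 10), 36 for (0, 0.5, 10), 37 for (0, 1, 10), 45 for (0, 5, 10).

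The text names the ANOVA but does not identify the pattern used.

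**2. The SD between means.** Let SS be the sum of squared deviations of the three means from their average.
- (0, 5, 10): SS = 25 + 0 + 25 = 50. SD = √(50/3) = 4.08, or √(50/2) = 5.00 with divisor k − 1.
- (0, 0, 10): SS = 11.11 + 11.11 + 44.44 = 66.67. SD = √(66.67/3) = 4.71, or √(66.67/2) = 5.77.

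These are the minimum and maximum for a range of 10. Taken literally, 14.6 gives SS = 3 × 14.6² = 639.5 and needs 5 per group (7 with divisor k − 1), not 36. Read as a variance of means it gives 51 (or 76), which does not match either.

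**3. ANOVA power at the planned size.** Noncentrality λ = n × SS/15², with 2 and 3(n − 1) degrees of freedom.

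| Means | SS | λ at 36 | Power, 36 per group | Power, 40 per group |
|---|---|---|---|---|
| (0, 0, 10) | 66.67 | 10.67 | 83.0% | 87.0% |
| (0, 0.5, 10) | 63.50 | 10.16 | 81.0% | 85.3% |
| (0, 1, 10) | 60.67 | 9.71 | 79.1% | 83.5% |
| (0, 2, 10) | 56.00 | 8.96 | 75.6% | 80.3% |
| (0, 5, 10) | 50.00 | 8.00 | 70.4% | 75.4% |

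At 36 per group the figure drops below 80% once the third mean is about 1 point from its neighbour. The 40-per-group column assumes that nobody is lost.

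**4. Tukey power for a 10-point pair.** At n = 36 the critical value is 3.362/√2 = 2.377 on 105 degrees of freedom. The noncentrality is 10/(15 × √(2/36)) = 2.828. Power is 67.4%. At 40 per group it is 72.8%. Reaching 80% takes 47 per group.

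**5. What baseline adjustment could recover.** With correlation r, the residual SD is 15 × √(1 − r²), if 15 is the unadjusted follow-up SD. At 36 per group:

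| Assumed r | Residual SD | ANOVA, (0, 5, 10) | Tukey, 10-point pair |
|---|---|---|---|
| 0 | 15.00 | 70.4% | 67.4% |
| 0.3 | 14.31 | 74.7% | 72.1% |
| 0.4 | 13.75 | 78.3% | 76.0% |
| 0.45 | 13.40 | 80.5% | 78.4% |
| 0.5 | 12.99 | 83.0% | 81.1% |

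**The case against.** The best defence is that these are labelling slips around a sound number. The 14.6 is close to the 15 used in the next sentence and may simply be a within-group SD with the wrong name, and nobody would read a β of 0.80 as 20% power. Both readings are plausible, though the first is an inference the text does not confirm. The entries still need correcting, because the SD between means is the effect-size input of an ANOVA calculation.

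Three further inferences are tempting, and the documents do not support them.

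- *That 36 is a two-group calculation passed off as an ANOVA.* It equals the two-group formula, but an ANOVA with means (0, 0.5, 10) gives the same number, and the text refers to several simulated scenarios. Its origin cannot be established.
- *That the 80% ANOVA power is simply not achieved.* If both operations work equally well, or if only one works, two means coincide and power at 36 per group is 83%. The shortfall depends on the pattern of means.
- *That the protocol promises 80% for the Tukey tests.* The figure stands beside the one-way ANOVA only. Powering the global test and following it with post-hoc comparisons is a common choice.

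It is also fair that the planned ANCOVA makes an unadjusted calculation conservative. This stands, but how much it helps depends on a correlation the article does not state, so neither a deficit nor its absence can be shown.

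**Conclusion.** The concern holds in a limited form. The SD between means of 14.6 is impossible next to a largest difference of 10, and 0.80 is the power, so β is 0.20. These two points need no assumption.

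The 80% is conditional. With SD 15 as the within-group SD and 36 per group, ANOVA power runs from 70% to 83% depending on the third mean, or from 75% to 87% if all 40 per group are retained. The stated figure therefore rests on a favourable pattern of means that the protocol does not state. A 10-point Tukey comparison has about 67% power at 36 per group and 73% at 40, before baseline adjustment.

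This is a fault in the justification of the sample size. It does not invalidate the planned analysis or affect its type I error, and it does not show that the trial is too small.

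**What to change.** Rewrite the Sample size paragraph and leave N as it is.

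1. Replace 14.6 with the SD between means that belongs to the assumed pattern (4.08 for equally spaced means, 4.71 if two are equal; name the divisor). If 14.6 was meant as a within-group SD, label it so and reconcile it with the 15 used in the calculation.
2. Write power = 0.80, β = 0.20.
3. State the assumed pattern of the three means.
4. Restate the power at 36 per group: 70% to 83% for the ANOVA across patterns, and about 67% for a 10-point Tukey comparison. Alternatively, state an assumed baseline correlation with its justification and give the ANCOVA-based power. About 0.45 restores 80% for the least favourable ANOVA pattern, and about 0.5 does so for Tukey.

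The cost is a few sentences and a less favourable power statement; no patients are added. Tukey's test can stay. Replacing it with a closed testing procedure is a separate trade-off, which would give up matching simultaneous confidence intervals, and is not part of this correction.

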### Planned statistical analysis

Treatment groups will be examined for comparability at baseline with respect to demographic and prognostic factors. All eligible patients, regardless of their compliance with protocol (analysis by intention-to-treat) will be included in the main analyses. To asses the effect of the interventions on the endpoints (six and 24 months), analysis of covariance (ANCOVA) will be performed using the baseline values as one of the covariates. Standard regression assumptions will be assessed using diagnostic plots, Jacknife residuals, Cook's distances, and Variance inflation Factor (VIF). We will adjust for an eventual imbalance at the baseline. Corresponding post-hoc tests (Tukey's test) will be performed. To evaluate the time-course at three, six, 12, and 24 months, repeated measures will be analyzed using linear mixed models. If the number of missing values exceeds 10% in one of the groups, multiple imputations will be used to estimate the missing values. To assess the robustness of our findings the analysis will be performed with and without the imputed values.

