### Outcome assessment

Baseline data will include gender, age, smoking, previous treatment, duration of symptoms, MR arthrography and conventional x-rays including outlet view, and primary and secondary outcome measures.

The same blinded observer will assess all participants after the procedure at three, six, 12 and 24 months. Pain, health related quality of life, complications, and a return to sports and work will be assessed at each time point. Blinding will be evaluated by asking the patients about which treatment they perceive to have received.

Pain during activity and pain at rest (over the last week) will be measured on a 0-100 visual analogue scale (VAS), comprising a horizontal line labelled no pain at one end and worst imaginable pain at the other end.

A range of standardised, generic and specific self-report health-related quality of life measures and the clinical Rowe Score will be used. To our knowledge outcome measures have not been particularly evaluated for patients with SLAP lesions. The primary outcome measures in the present trial will be the 1988 version of the Rowe Score [18] and the Western Ontario Instability Index (WOSI)[19]. The latter has been professionally translated to Norwegian.

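### Observed baseline imbalance is a poor trigger for covariate adjustment; with prognostic covariates it makes the test conservative, and a short list fixed in advance would be better

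*Protocol article*

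**What the plan says.** The section Planned statistical analysis in the protocol article contains three relevant statements.

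- Baseline comparison: "Treatment groups will be examined for comparability at baseline with respect to demographic and prognostic factors".
- Main model at six and 24 months: "analysis of covariance (ANCOVA) will be performed using the baseline values as one of the covariates".
- Rule for further adjustment: "We will adjust for an eventual imbalance at the baseline".

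The section Outcome assessment lists what is available for adjustment: "Baseline data will include gender, age, smoking, previous treatment, duration of symptoms", followed by imaging and the outcome measures themselves. The section Randomisation describes permuted blocks and names no stratification factor that would tie particular covariates to the design.

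**The concern.** In a randomised trial, whether to adjust for a variable should depend on whether it predicts outcome. The observed difference between arms carries little information about that. A rule triggered by imbalance brings in variables that happen to differ, whether or not they matter, and gives no reason to include prognostic variables that happen to be balanced.

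It also affects the standard error. A prognostic covariate left out of the model adds both to the chance error in the treatment estimate and to the residual variance, in matching proportion, so the test is valid. If the covariate enters only when it is imbalanced, the worst chance errors are removed. In all other trials the residual variance stays at its larger, unadjusted value. The standard error is then too large on average for the estimator in use, the test is conservative and some power is lost. In a three-arm trial of 120 patients that loss is avoidable.

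A later analysis plan that named candidate variables or a cut-off would not by itself remove the problem, because the printed trigger would still be the observed imbalance.

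**Working it through.** **The plan's own figure.** The section Sample size assumes "Assuming that the largest difference between treatments will be 10 units" with "SD = 15, α = 0.05, β = 0.80, One-Way ANOVA" (the 0.80 is evidently power) and concludes "our study will require 36 patients in each group". The two-group normal formula reproduces this: n = 2 x (1.960 + 0.842)^2 x 15^2 / 10^2 = 35.3, so 36. The planned total follows from "Assuming some patients drop-out, we plan to include 40 patients in each group": 36 / 0.90 = 40 per group, 120 in all. A three-group one-way ANOVA with SD 15 gives 34 per group for means 0, 0, 10 and 45 for means 0, 5, 10. The sample size does not depend on the present point; it only sets the size of the simulated trial.

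**Simulation.** No treatment effect, 3 x 40 patients, 8,000 trials per scenario, ANCOVA with the baseline outcome always in the model.

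Inputs from the protocol: three arms, 40 per arm, alpha 0.05, baseline outcome as a covariate.

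Assumptions not in the protocol:
- four independent candidate covariates;
- each correlated r with the outcome;
- under the imbalance rule, a covariate is added if its baseline ANOVA p-value is below a screen of 0.05 or 0.20.

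The covariates together explain 4 x r^2 of the outcome variance: 4 x 0.3^2 = 0.36 for r = 0.3, and 4 x 0.45^2 = 0.81 for r = 0.45. The second is an extreme case.

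| r of each covariate | r of baseline outcome | Screen | Any covariate added | Type I error, fixed set | Type I error, imbalance rule | Coverage, imbalance rule |
|---|---|---|---|---|---|---|
| 0.3 | 0.5 | 0.05 | 17.8% | 0.052 | 0.039 | 0.958 |
| 0.3 | 0.5 | 0.20 | 58.4% | 0.047 | 0.029 | 0.969 |
| 0.45 | 0.3 | 0.05 | 19.5% | 0.048 | 0.031 | 0.968 |
| 0 | 0.5 | 0.05 | 17.5% | 0.052 | 0.051 | 0.949 |

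Coverage refers to a nominal 95% interval. With the fixed set it was 0.948 to 0.954.

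**Checks.**
- How often a covariate is added agrees with the closed form: 1 - 0.95^4 = 18.5% and 1 - 0.80^4 = 59.0%.
- The Monte Carlo standard error at 0.05 is sqrt(0.05 x 0.95 / 8000) = 0.0024, so 0.039 lies about 4.6 standard errors below nominal.
- A repeat run under similar assumptions gave about 0.027 to 0.035 for the imbalance rule with prognostic covariates, 0.051 without, and about 0.044 to 0.055 for the fixed set.

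**Where the conservatism comes from.** With r = 0.3, the residual variance is 1 - 0.5^2 = 0.75 without the four covariates and 0.75 - 0.36 = 0.39 with them. At the 0.05 screen about 82% of trials add nothing and keep the larger value.

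**Upper bound if covariates were picked for the result.** Taking the smallest p-value over all subsets of the four covariates gives a type I error of 0.160 to 0.283 with prognostic covariates and 0.068 with unrelated ones.

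**The case against.** Much can be said for the plan. The baseline outcome score, probably the most useful covariate, is in the model unconditionally. Calling it one among several covariates suggests that others may be fixed in documents not shown. The comparability check refers to prognostic factors, so prognosis is not ignored. The absence of a variable list or threshold is detail that an article normally leaves to the full protocol or analysis plan, and it is not held against the plan here. All of this stands, and it limits the point to the printed trigger.

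A reader might infer four stronger things that the document does not support.

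- *The p-value and interval generally lose their properties.* They do not: with covariates unrelated to outcome both are nominal. The article also states no confidence level, so only nominal coverage can be discussed.
- *The rule inflates false positives.* Applied mechanically it does the opposite. The 0.160 to 0.283 range needs a deliberate choice of the most favourable subset, which the protocol does not set out.
- *The model is chosen after unblinding.* The text does not say when imbalance is judged; it could be judged under coded arms, before outcomes are available.
- *The chance of flagging a variable measures the harm.* With 5% tests on independent variables, at least one of five is flagged in 1 - 0.95^5 = 23% of trials, and at least one of ten in 1 - 0.95^10 = 40%. These are frequencies of use, not changes in error rate or coverage. The protocol names no such test, and the outcome scores overlap too much to be independent.

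It may also be argued that the imbalance-adjusted model is only supplementary. The text leaves that open, but the sentence stands between the model diagnostics for the ANCOVA and its post-hoc tests, so the natural reading is that it modifies the main model.

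**Conclusion.** The point holds in a limited form. The protocol states a selection rule based on chance imbalance, and a prespecified set is better. If the added covariates are prognostic and the rule is applied mechanically, type I error falls to about 0.03 to 0.04 against 0.05 and intervals are too wide. If they are not prognostic, nothing is distorted.

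The size rests on the assumed number, independence and strength of covariates and on the assumed screens. The departure shrinks as the correlations approach zero, and the lower end needs a lenient screen or very strong covariates. The direction does not rest on the exact values. This is a modest loss of efficiency that is cheap to avoid, and does not threaten the trial's validity.

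**What to change.** Replace the sentence with a statement that the six- and 24-month ANCOVA will include the baseline value of the outcome and a short list of prognostic covariates, whatever the observed balance. The list should come from variables already collected, for example age, gender and duration of symptoms, and be fixed before any outcome data are seen. The baseline comparison can stay as a description of the groups. Any adjustment prompted by an observed imbalance should be reported only as a labelled sensitivity analysis.

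The cost is one sentence and no new data. With 36 analysed per arm, 3 x 36 - 3 = 105 degrees of freedom remain after the arm means. The baseline outcome, already planned, takes one, leaving 104; three further covariates of one degree each leave 101. If a chosen covariate turns out not to be prognostic, little more than its degree of freedom is lost. The sample size of 36, or 40 with dropout, is unaffected.

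### Imputation only above 10% missing lets up to 4 of 40 patients per arm leave the intention-to-treat endpoint ANCOVA with no missing-data sensitivity analysis

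*Protocol article*

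**What the plan says.** All the analysis text is in the Planned statistical analysis section of the protocol article.

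- **Analysis set:** "All eligible patients, regardless of their compliance with protocol (analysis by intention-to-treat) will be included in the main analyses".
- **Endpoint model:** for the effect at six and 24 months, "analysis of covariance (ANCOVA) will be performed using the baseline values as one of the covariates".
- **Time course:** "To evaluate the time-course at three, six, 12, and 24 months, repeated measures will be analyzed using linear mixed models".
- **Missing data:** "If the number of missing values exceeds 10% in one of the groups, multiple imputations will be used to estimate the missing values".
- **Robustness:** "To assess the robustness of our findings the analysis will be performed with and without the imputed values".

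The Sample size section requires 36 patients per group and then adds: "Assuming some patients drop-out, we plan to include 40 patients in each group". It gives no drop-out rate.

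**The concern.** An ANCOVA at one time point omits anyone without a score at that time point, and the article gives no other handling when missingness is at or below 10%. The analysis is then a complete-case analysis under an intention-to-treat label. A small proportion missing does not show that the missingness is harmless.

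The robustness sentence does not cover this situation. With no imputation there is nothing to compare, so the safeguard is absent exactly where patients are omitted. When the rule does fire, both versions are produced, but the text does not say which one leads.

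The cut-off also lies where the trial expects to be. If losses match the implied allowance, one further missing patient in one arm changes how the main analysis is done for all three arms, and the method can differ between 6 and 24 months. The bias at stake arises if loss is related to how a patient is doing, which is plausible in a sham-controlled surgical trial followed for two years. The complete-case ANCOVA adjusts for baseline but not for the scores collected at the visits in between.

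**Working it through.** **Inputs from the document.** Planned 40 per group, three groups; 36 evaluable per group; SD 15; important difference 10 points on the Rowe Score; imputation if more than 10% missing in one group.

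**Assumed, not in the document.** True loss rates of 5% to 12%; independent losses between patients; the 10% counted per outcome and per visit (the rule does not say how it is counted); and the score gap between patients who leave and those who stay.

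**1. The plan's own figure.** The two-group normal formula with difference 10, SD 15, two-sided alpha 0.05 and power 0.80 (the article prints 0.80 as beta) gives 2 × (1.960 + 0.842)² × 15² / 10² = 35.3, rounded up to 36 per group. This matches the article. A three-group ANOVA with means 0, 0, 10 gives 34, which is close.

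**2. Implied allowance.** 1 − 36/40 = 0.10, and 36/0.90 = 40. So the allowance is 10%, the same value as the imputation threshold.

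**3. What the threshold means in patients.** 4/40 = 10.0% does not exceed 10%; 5/40 = 12.5% does. Up to 4 per arm, or 3 × 4 = 12 of 120, can be absent with no imputation.

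**4. Chance that the rule fires at one visit.** Let X be the number missing in an arm, X ~ Bin(40, p), and q = P(X ≥ 5). The chance for at least one of three arms is 1 − (1 − q)³.

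| Assumed true loss p | q, one arm | At least one of three arms |
|---|---|---|
| 5% | 0.048 | 1 − 0.952³ = 0.14 |
| 8% | 0.213 | 1 − 0.787³ = 0.51 |
| 10% | 0.371 | 1 − 0.629³ = 0.75 |
| 12% | 0.533 | 1 − 0.467³ = 0.90 |

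Between 5% and 12% loss, the method for the main analysis runs from probably complete-case to probably imputed. At the implied 10%, it stays complete-case in about 25% of cases.

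**5. Possible bias without imputation.** If a fraction f of one arm is lost and those patients would have scored d points worse than the rest, the complete-case mean of that arm is too favourable by f × d.

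- d = 7.5 (half an SD): 0.10 × 7.5 = 0.75 points.
- d = 15 (one SD): 0.10 × 15 = 1.5 points, which is 1.5/10 = 15% of the important difference.

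For scale, the standard error of a two-arm difference with 36 per arm, before baseline adjustment, is 15 × √(2/36) = 3.5 points. The larger bias is therefore about 1.5/3.5 = 0.4 of a standard error.

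**The case against.** The case for leaving the rule alone has some force.

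- **The rule is prespecified and looks at counts of missing values, not at outcomes or effects.** That is true, so it would be wrong to infer that the estimator is picked by its result. The method is still unknown until the losses are counted.
- **Both versions are reported when imputation is used.** This stands above the threshold. It gives nothing at or below it, and it does not say which version is the main result.
- **A per-group trigger suits lopsided loss.** It would catch heavy loss from one arm, such as dissatisfied sham patients. It would not catch four such patients.
- **The 10% loss is not stated.** Correct. It is worked back from 36 and 40, which could simply be rounding, and the 75% depends on it. That is why a range of loss rates is shown.
- **The remedy is partial.** A mixed model recovers only what observed scores predict. Only the 3-month score precedes the 6-month endpoint, and a patient lost before three months contributes no follow-up score. This stands.
- **Omission is inferred.** The article does not say that patients without a score are left out. It follows from using ANCOVA at a single time point with no other handling given.

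Two stronger readings are tempting but not supported. A reader might infer that, with two models giving 6- and 24-month effects, the plan does not say which one counts. It does: ANCOVA serves the endpoints and the mixed model the time course. A reader might also infer that restricting the analysis to eligible patients allows removal after randomisation. The Randomisation and Interventions sections place arthroscopic confirmation immediately before the envelope is opened, and the analysis is declared intention-to-treat whatever the compliance. Nothing provides for later removal.

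**Conclusion.** The point holds as a weakness in a rule that the article fixes, not as a detail left for a fuller plan. At or below 10% missing, up to 4 of 40 patients per arm leave an endpoint analysis described as intention-to-treat, and no missing-data sensitivity analysis is available. Above 10%, two analyses exist and neither is named as leading.

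The size is modest: 0.75 to 1.5 points on the Rowe Score in the illustration, against an important difference of 10. That rests on an assumed gap of 7.5 to 15 points between leavers and stayers and on the full 10% being lost in one arm. The chance of crossing the threshold, 14% to 90%, rests on assumed loss rates of 5% to 12%. The change is still worth making, because it is cheap and gives one main analysis that does not depend on how many scores turn out to be missing.

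**What to change.** Delete the 10% trigger. Estimate the 6- and 24-month contrasts for all randomised patients in their allocated arm, whatever the missing rate, by one of two routes, and name that route as primary:

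- the linear mixed model already planned, adjusted for baseline and with a treatment-by-visit term, with the contrasts taken at 6 and 24 months; or
- ANCOVA after multiple imputation that draws on the 3-, 6- and 12-month scores.

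Report complete-case ANCOVA as a sensitivity analysis in every case.

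The cost is a change of wording and slightly more analysis work. No new data are needed, and 40 per group stands. Both routes rely on the scores being missing at random given what was observed, and they would remove only part of any bias from loss related to outcome.
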